***Surveillance period for occurrence of adverse events***

All adverse events occurring within one month (minimum 30 days) following administration of each dose of vaccine/comparator must be recorded on the Adverse Event form in the subject's CRF, irrespective of severity or whether or not they are considered vaccination-related.

Additionally, all serious adverse events (see Section 8.5) occurring during the period starting from the day of administration of the first dose of study vaccine/comparator to each subject and ending within 19 months following administration of the last dose of study vaccine/comparator for that subject must be recorded. See Section 8.5.2 for instructions for reporting and recording of serious adverse events.

Instances of death, cancer or congenital abnormality in offspring if brought to the attention of the investigator AT ANY TIME after cessation of study AND suspected by the investigator to be related to study vaccine, should be reported to the Study Contact for Reporting Serious Adverse Events (see Section 8.5.2).

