**(Amended January 17, 2003)**

Paediatric dose (0.25 ml dose volume) of the RTS,S/AS02A candidate malaria vaccine will be administered at each vaccination. Full doses (0.5 ml dose volume) of hepatitis B vaccine (Engerix-B™), the 7-valent pneumococcal conjugate vaccine (Prevnar®) and *Haemophilus influenzae* type b vaccine (Hiberix™) will be given to the control group.

Subjects who cannot be vaccinated on the originally scheduled date due to an acute illness (on the judgement of the investigator or designate) or scheduling conflicts will be vaccinated within 7 days and undergo all study procedures for this visit on the same day as vaccination. In the particular case of any child found to be febrile (axillary temperature   37.5°C), a blood slide will be taken to investigate malaria parasitaemia. Children will be treated as appropriate for their condition and will be followed up until resolution of any symptoms and be vaccinated if their clinical symptoms resolve within 7 days.

Those who cannot be re-vaccinated within 7 days of their scheduled date will continue all study procedures apart from receiving further study vaccinations.

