***Recording adverse events***

At each visit/assessment, all adverse events either observed by the investigator or one of his clinical collaborators or reported by the subject’s parent/guardian spontaneously or in response to a direct question will be evaluated by the investigator. Adverse events not previously documented in the study will be recorded in the Adverse Event form within the subject's CRF. The nature of each event, date and time (where appropriate) of onset, outcome, intensity and relationship to vaccination should be established. Details of any corrective treatment should be recorded on the appropriate page of the CRF. See Section 8.5.2 for instructions for reporting and recording of serious adverse events.

As a consistent method of soliciting adverse events, the subject or their legal representative should be asked a non-leading question such as:

"Has your child acted differently or felt different in any way since receiving the vaccine or since the last visit?"

N.B. The investigator should record only those adverse events having occurred within the time frames defined above.

Adverse events already documented in the CRF, i.e. at a previous assessment, and designated as ‘ongoing’ should be reviewed at subsequent visits, as necessary. If these have resolved, the documentation in the CRF should be completed. N.B. If an adverse event changes in frequency or intensity during a study period, a new record of the event will be started.

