### Reporting serious adverse events

Serious Adverse Events will be reported in a prospective manner during the period starting from the day of administration of the first dose of study vaccine to each subject and ending with the last study visit or performance of the last study procedure or within one month (minimum 30 days) following administration of the last dose of study vaccine for that subject, whatever is longer. Any serious adverse events occurring during this period, whether or not considered to be related to the study vaccine must be reported by the investigator to the appropriate Clinical Safety Group within 1 calendar day (i.e. 24 hours of initial receipt) within GSK Biologicals and MVI, and to the Local Safety Monitor or within 3 calendar days if this period includes a weekend or public holiday.

The investigator will document all available information regarding the serious adverse event on the Serious Adverse Event pages contained in the individual Case Report Form and fax to the GSK Biologicals and MVI Contacts for Serious Adverse Event Reporting. The investigator should not wait to receive additional information to fully document the event before notifying GSK Biologicals and MVI of a serious adverse event. This initial notification should include, as a minimum, sufficient information to permit identification of:

- the reporter
- the subject
- study vaccine(s)
- adverse event(s)
- date of onset

In the event of a death or a serious adverse event determined by the investigator to be related to vaccination, receipt of the fax must be confirmed by telephone call.

The initial fax report should be followed by a full summary utilising the GSK Biologicals Serious Adverse Event pages in the individual Case Report Form detailing relevant aspects of the adverse events in question. Where applicable, information from relevant hospital case records and autopsy reports should be obtained.

***A post-study AE/SAE is defined as any event that occurs outside of the AE/SAE surveillance period for occurrence of adverse events (defined in Section 8.1). Investigators are not obligated to actively seek AEs or SAEs in former study participants.***

***If the investigator learns of any SAE, including a death, at any time after a subject has been discharged from the study, and he/she considers the event reasonably related to a study vaccine, the investigator will promptly notify the Study Contact for Reporting SAEs.***

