***Safety***

- Occurrence of serious adverse events during the single-blind surveillance period (from month 8½ to month 21).

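### Section 8.1 closes SAE recording 19 months after each child's own last dose, which falls short of month 21 for children who stop vaccination early and conflicts with section 8.5.2

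*Supplement*

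**What the plan says.** All references are to the protocol as amended in January 2003.

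- **Section 8.1, surveillance period.** SAE recording starts with the first dose and is described as "ending within 19 months following administration of the last dose of study vaccine/comparator for that subject must be recorded".
- **Section 8.1, recording.** A note restricts what is entered: "The investigator should record only those adverse events having occurred within the time frames defined above".
- **Section 8.5.2, first paragraph.** SAE reporting is described as "ending with the last study visit or performance of the last study procedure or within one month (minimum 30 days"), the month being counted from the child's final dose, and the later of these applies. SAEs in this period are reported whether or not they are thought related.
- **Section 8.5.2, amended text.** A post-study AE or SAE "is defined as any event that occurs outside of the AE/SAE surveillance period for occurrence of adverse events (defined in Section 8.1"). For these, "Investigators are not obligated to actively seek AEs or SAEs in former study participants", and notification is asked for only when the investigator considers the event reasonably related.
- **Section 5.2.2.** Children who cannot be vaccinated within 7 days of the scheduled date "will continue all study procedures apart from receiving further study vaccinations".
- **Section 10.4.2 (Cohort 2 safety endpoint).** "Occurrence of serious adverse events during the single-blind surveillance period (from month 8½ to month 21"). The synopsis gives Cohort 1 the same period. Section 10.4.1 gives a different start for Cohort 1 (month 10) but the same end.
- **Section 10, data lock points.** Month 21 is day 630.
- **Section 5.2.8.** Monthly home visits for SAEs run for 18 months from 60 days after the last vaccination, labelled day 120.
- **Sections 5.4 and 5.6.** SAE reporting is listed at the field visits of months 9 to 21 and at clinic visit 7, with no exception for children who missed doses.

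**The concern.** The SAE endpoint ends on a study date common to all children. The recording rule in 8.1 ends on a date that depends on how many doses the child received. The two agree for a child with three doses and part for a child with one or two. Section 5.2.2 keeps such children under follow-up.

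The amendment gave 8.1 a second role. It now also decides which events are post-study, and so which events need not be sought and are notified only if judged related. If site staff follow 8.1 and its note, an unrelated SAE in the last weeks of follow-up of an early stopper goes unrecorded. If they follow the first paragraph of 8.5.2, it is reported. Safety recording in children whose vaccination was interrupted should not depend on which paragraph is read.

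Section 8.1 also keeps an older post-study paragraph limited to death, cancer or congenital abnormality in offspring. Amendment 2 records that the DSMB found the congenital-abnormality requirement inappropriate for children of this age. It was struck from 8.5.2, but its counterpart in 8.1 remained.

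**Working it through.** **Inputs.** Doses on days 0, 30 and 60, and visit windows of 27–37, 27–37, 30–37 and (visit 5 to visit 7) 512–568 days (sections 5.3 and 5.5). Month 21 = day 630 (section 10). Month 21 is also called 19 months after dose 3 (section 10.4.1).

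**1. The protocol's own date.** With 30-day months, dose 3 + 19 months = 60 + 19 × 30 = 630, and 21 × 30 = 630. Day 630 is reproduced exactly. With 30.4375-day months, 60 + 578.3 = 638.3, which does not reproduce it. The protocol's day counts therefore use 30-day months.

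**2. Close of the 8.1 period by last dose.** Gap = 630 − (day of last dose + 570).

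| Last dose received | 8.1 period closes | Gap to day 630 |
| --- | --- | --- |
| Dose 1 (day 0) | day 570 | 60 days |
| Dose 2 (day 30) | day 600 | 30 days |
| Dose 3 (day 60) | day 630 | 0 days |

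**3. Month length.** With 30.4375-day months on both sides, month 21 is day 639.2 and the gaps are 60.9, 30.9 and 0.9 days. Setting 19 calendar months (578 days) against day 630 gives 52 and 22 days, but that mixes two conventions. On either consistent convention the gap is about two months or one month.

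**4. Actual date of visit 7.** Earliest: 27 + 27 + 30 + 512 = day 596. Latest: 37 + 37 + 37 + 568 = day 679. If a child with dose 1 only keeps these windows, visit 7 falls 596 − 570 = 26 to 679 − 570 = 109 days after the 8.1 period closes. For a child with three doses, visit 7 falls 30 + 512 = 542 to 37 + 568 = 605 days after dose 3, so at most 605 − 570 = 35 days after the period closes.

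**5. Home visits in 5.2.8.** For three doses: day 120, and the 18th monthly visit at 120 + 17 × 30 = day 630. Read literally from the last vaccination, a child with dose 1 only starts on day 60 and has the 18th visit at 60 + 17 × 30 = day 570. With two doses the dates are day 90 and day 600. The day-120 label fits three-dose children only, and the literal rule repeats the shortfall in step 2.

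**6. One event under each rule.** Take an SAE on day 590, judged unrelated, in a child who had dose 1 only and is still in follow-up.

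| Rule | Treatment of the event |
| --- | --- |
| 8.1 with its note | Outside the period; not recorded |
| 8.5.2, first paragraph | Reportable |
| 8.5.2, amended definition | Post-study; notification asked for only if related |
| 5.4 and 5.6 schedules | Collected at the next field visit or at visit 7 |
| Synopsis and 10.4 endpoint | Falls inside the period |

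**The case against.** The strongest reply is that 8.1 itself refers the reader to 8.5.2 for reporting and recording SAEs, and that the first paragraph of 8.5.2 reaches the last visit whatever the number of doses. The schedules place SAE reporting at every field visit to month 21 and at visit 7. The relaxed post-study duty is worded for former participants and for subjects already discharged, and a child still receiving home visits is neither. All of this stands. It is why a reader who infers that early stoppers actually leave SAE recording goes further than the documents allow.

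It does not remove the conflict. The note in 8.1 is restrictive, and the definition of a post-study event in 8.5.2 rests on the 8.1 period and not on discharge.

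Three further inferences are tempting and unsupported:

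- **A bias between arms.** No figures on stopping by arm are given, and section 10.7.3 plans a description of SAEs with no comparison of rates.
- **A count of lost child-time.** The sample-size allowances give 0.10 × 1564 + 0.20 × 416 = about 240 non-evaluable children. These allowances include dropouts, who have no late follow-up to lose, so they do not count early stoppers who remain.
- **Lost endpoint time in fully vaccinated children.** With dose 3 on day 60 the 8.1 period reaches day 630. A late visit 7 falls after that date, and 8.5.2 still covers it. Only the disagreement between the two sections applies to these children.

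Children with an absolute contraindication come under section 4.6, where continuing other procedures is at the investigator's discretion. The point applies to them only if they continue.

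**Conclusion.** The point holds as a contradiction between operative rules. The 8.1 period closes about 60 days before the end of the SAE endpoint for a child who stops after dose 1, and about 30 days before for one who stops after dose 2. This assumes doses on the nominal days, 30-day months, and a child who remains in follow-up. In that gap the same SAE is reportable under one paragraph of 8.5.2 and post-study under another. The end-date sentence in 8.5.2 is not marked as amended; the conflict became operative when the amended text tied the definition of post-study events to 8.1.

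No loss of data is demonstrated, the number of children concerned is unknown, and no effect on the comparison of arms is shown. The matter is minor in size, but it concerns a safety-recording rule that disagrees with its own endpoint.

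**What to change.** 1. In 8.1 and 8.5.2, state one end of SAE recording: the month-21 visit (clinic visit 7) for every child still in follow-up, whatever the number of doses received.
2. In 8.5.2, define a post-study event by that same end.
3. In 5.2.8, fix the start and end of the monthly home visits by study day for all children, so that they no longer depend on the last vaccination and agree with the schedules.
4. Delete the 8.1 paragraph limited to death, cancer or congenital abnormality, leaving the amended 8.5.2 rule (any SAE considered related, including death) as the only post-study rule. Section 8.5.1 already has cancers reported in the same way as SAEs.

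The cost is protocol wording. The home visits to month 21 and visit 7 are already scheduled, so no visit, sample or child is added.

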***Recording adverse events***

At each visit/assessment, all adverse events either observed by the investigator or one of his clinical collaborators or reported by the subject’s parent/guardian spontaneously or in response to a direct question will be evaluated by the investigator. Adverse events not previously documented in the study will be recorded in the Adverse Event form within the subject's CRF. The nature of each event, date and time (where appropriate) of onset, outcome, intensity and relationship to vaccination should be established. Details of any corrective treatment should be recorded on the appropriate page of the CRF. See Section 8.5.2 for instructions for reporting and recording of serious adverse events.

As a consistent method of soliciting adverse events, the subject or their legal representative should be asked a non-leading question such as:

"Has your child acted differently or felt different in any way since receiving the vaccine or since the last visit?"

N.B. The investigator should record only those adverse events having occurred within the time frames defined above.

Adverse events already documented in the CRF, i.e. at a previous assessment, and designated as ‘ongoing’ should be reviewed at subsequent visits, as necessary. If these have resolved, the documentation in the CRF should be completed. N.B. If an adverse event changes in frequency or intensity during a study period, a new record of the event will be started.

### Solicited adverse events

**Local (injection site) adverse events**

- Pain at injection site
- Swelling at injection site

**General adverse events**

- Fever (defined as axillary temperature  37.5°C)
- Drowsiness
- Loss of appetite
- Irritability / fussiness

## Assessment of intensity

Intensity of the following adverse events should be assessed as described:

| **Adverse Event** | **Intensity grade** | | **Parameter** | |
| --- | --- | --- | --- | --- |
| Pain at injection site | 0 | | Absent | |
|  | 1 | | Minor reaction to touch | |
|  | 2 | | Cries/protests on touch | |
|  | 3 | | Cries when limb is moved/spontaneously painful | |
| Swelling at injection site | |  | Record greatest surface diameter in mm | |
| Fever* | |  | | Record temperature in °C |
| Irritability/Fussiness | 0 | | Behavior as usual | |
|  | 1 | | Crying more than usual/ no effect on normal activity | |
|  | 2 | | Crying more than usual/ interferes with normal activity | |
|  | 3 | | Crying that cannot be comforted/ prevents normal activity | |
| Drowsiness | 0 | | Behavior as usual | |
|  | 1 | | Drowsiness easily tolerated | |
|  | 2 | | Drowsiness that interferes with normal activity | |
|  | 3 | | Drowsiness that prevents normal activity | |
| Loss of appetite | 0 | | Normal | |
|  | 1 | | Eating less than usual/ no effect on normal activity | |
|  | 2 | | Eating less than usual/ interferes with normal activity | |
|  | 3 | | Not eating at all | |
| *Fever is defined as axillary temperature  37.5°C. | | | | |

The maximum intensity of local injection site swelling will be scored at GSK Biologicals as follows:

| 0 | : | none |
| --- | --- | --- |
| 1 | : | < 5 mm |
| 2 | : | 5 - 20 mm |
| 3 | : | > 20 mm |

The maximum intensity of fever will be scored at GSK Biologicals as follows:

| 0 | : | < 37.5°C |
| --- | --- | --- |
| 1 | : | 37.5 – 38.0°C |
| 2 | : | > 38 – 39.0°C |
| 3 | : | > 39.0°C |

For all other adverse events, maximum intensity should be assigned to one of the following categories:

| 0 | = | No adverse event |
| --- | --- | --- |
| 1 | = | An adverse event which is easily tolerated by the subject, causing minimal discomfort and not interfering with everyday activities. |
| 2 | = | An adverse event which is sufficiently discomforting to interfere with normal everyday activities |
| 3 | = | An adverse event which prevents normal, everyday activities. (In a child, such an adverse event would, for example, prevent prevent attendance at school/ kindergarten/ a day-care center and would cause the parents/ guardians to seek medical advice). |

## Assessment of causality

Every effort should be made by the investigator to explain each adverse event and assess its causal relationship, if any, to administration of the study vaccine(s).

The degree of certainty with which an adverse event can be attributed to administration of the study vaccine(s) (or alternative causes, e.g. natural history of the underlying diseases, concomitant therapy, etc.) will be determined by how well the event can be understood in terms of one or more of the following:

- Reaction of similar nature having previously been observed with this type of vaccine and/or formulation.
- The event having often been reported in literature for similar types of vaccines.
- The event being temporally associated with vaccination or reproduced on re-vaccination.

All solicited local (injection site) reactions will be considered causally related to vaccination. Causality of all other adverse events should be assessed by the investigator using the following method:

In your opinion, did the vaccine(s) possibly contribute to the adverse event?

| NO | : | The adverse event is not causally related to administration of the study vaccine(s). There are other, more likely causes and administration of the study vaccine(s) is not suspected to have contributed to the adverse event. |
| --- | --- | --- |
| YES | : | There is a reasonable possibility that the vaccine contributed to the adverse event. |

Non-serious and serious adverse events will be evaluated as two distinct events given their different medical nature. If an event meets the criteria to be determined “serious” (see Section 8.1 for definition of serious adverse event), it will be examined by the investigator to the extent to be able to determine ALL contributing factors applicable to each serious adverse event.

Possible contributing factors include:

- Medical history
- Other medication
- Protocol required procedure
- Lack of efficacy of the vaccine
- Erroneous administration
- Other cause (specify)

## Following-up of adverse events and assessment of outcome

Investigators should follow-up subjects with serious adverse events until the event has resolved, subsided, stabilised, disappeared, the event is otherwise explained, or the subject is lost to follow-up; or, in the case of non-serious adverse events, the subject completes the study. Clinically significant laboratory abnormalities, as well as any adverse event, will be followed up until they have returned to normal, or a satisfactory explanation has been provided. Reports relative to the subsequent course of an adverse event noted for any subject must be submitted to the Study Monitor.

Outcome should be assessed as:

1 = Recovered

2 = Recovered with sequelae

3 = Ongoing at subject study conclusion

4 = Died

5 = Unknown

## Serious adverse events

### Definition of a serious adverse event

A serious adverse event is any untoward medical occurrence that results in death, is life threatening*, results in persistent or significant disability/incapacity† , requires in-patient hospitalisation‡ or prolongation of existing hospitalisation or is a congenital anomaly/birth defect in the offspring of a study subject. In addition, important medical events that may jeopardise the patient or may require intervention to prevent one of the other outcomes listed above should be considered serious. (Examples of such treatments are intensive treatment in an emergency room or at home for allergic bronchospasm; blood dyscrasias or convulsions that do not results in hospitalisation; or development of drug dependency or drug abuse.)

Although not considered as ‘serious adverse events’, cancers should be reported in the same way as serious adverse events.

*Life threatening—definition: An adverse event is life threatening if the subject was at risk of death at the time of the event; it does not refer to an event, which hypothetically might have caused death, if it were more severe.

†Disabling/incapacitating—definition: An adverse event is incapacitating or disabling if the event results in a substantial disruption of the subject's ability to carry out normal life functions. This definition is not intended to include experiences of relatively minor medical significance such as headache, nausea, vomiting, diarrhoea, influenza, and accidental trauma (e.g. sprained ankle).

‡Hospitalisation: In general, hospitalisation signifies that the subject has been detained (usually involving at least an overnight stay) at the hospital or emergency ward for treatment that would not have been appropriate in the physician’s office or out-patient setting.

Hospitalisation for either elective surgery related to a pre-existing condition which did not increase in severity or frequency following initiation of the study or for routine clinical procedures¶ (including hospitalisation for “social” reasons) that are not the result of an adverse event need not be considered as adverse events and are therefore not serious adverse events.

¶Routine Clinical Procedure—definition: One which is defined as a procedure which may take place during the study period and should not interfere with the study vaccine administration or any of the ongoing protocol specific procedures.

N.B. If anything untoward is reported during an elective procedure, that occurrence must be reported as an adverse event, either ‘serious’ or ‘non-serious’ according to the usual criteria.

When in doubt as to whether ‘hospitalisation’ occurred or was necessary, the adverse event should be considered serious.

